### Monitoring

The academic contract research organization (A-CRO) of the Clinical Trial Center, Daejeon Korean Medicine Hospital of Daejeon University, which is independent from the investigators and sponsor, and has no competing interests will form the data monitoring committee (DMC). The DMC will supervise the progress of the clinical trial and will review and confirm whether the trial is being conducted and recorded in accordance with the protocol, standard operating instructions, clinical trial management standards, and related regulations on a regular basis. Phone calls and visits will be employed for the monitoring process. Upon visit, the monitoring staff will evaluate the trial progress and inspect the original records of test subjects and data storage. Following a monitoring session, the investigators will receive a follow-up letter in 2 days. The monitoring report will be completed in seven days, reviewed, and approved in four days.

### Adverse events

Adverse events (AEs) refer to any harmful and unintended signs, symptoms, or diseases that occur in test subjects who have received a clinical trial intervention and do not necessarily have a causal relationship with the relevant intervention method. Serious adverse events (SAEs) refer to any of the following AEs that occur as a result of clinical trial intervention: (1) when death or a threat to life occurs, (2) when hospitalization is required or the hospitalization period must be extended, (3) when there is permanent or serious disability or functional decline. The subject who has developed an AE must be monitored by the test staff until the symptoms have subsided and his or her condition has stabilized. If there is a request from the client, a report on the progression of the AE must be submitted.

The principal investigator (PI) must explain to the test staff, subjects, and their guardians all possible AEs that may occur and train them to report any phenomena that appear after the intervention. All SAEs that occur during the study period must be reported to the PI within 24 hours, regardless of whether they are related to the intervention or not. If an SAE occurs, the PI must inform the client (Daejeon Korean Medicine Hospital of Daejeon University) promptly and provide comprehensive details in writing within 5 days. Clinical trials must be halted until further instructions are given. All serious and unexpected AEs must be disclosed immediately to other relevant investigators, the Institutional Review Board (IRB), and the Ministry of Food and Drug Safety (MFDS) within the specified time frame: (1) within 7 days of notification to the client for death or life-threatening AE, with additional detailed information provided within 8 days of the initial report date; (2) within 15 days of notification to the client for all other serious or unexpected AE. SAE must be documented in the report, and the following information should be included in the final report, if possible: data on the occurrence of the SAE, its severity, treatment, course, and causal relationship with the intervention.

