### Safety evaluation

To determine safety, lab test results will be compared to the baseline to identify any clinical changes. AE that occurred during the study period will be listed and thoroughly explained. All SAE will be thoroughly described. AE will be gathered through patient-reported symptoms and investigator-made observations. The frequency of AE associated with and unrelated to the intervention will be recorded and presented as descriptive statistics. If necessary, additional statistical analysis will be performed based on the nature of the variables and the purpose of the evaluation.

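### The SAE definition requires causation by the intervention, which contradicts the rule to report SAEs whether related or not; the AE definition does not clearly cover the usual-care arm

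*Protocol article*

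**What the plan says.** All references are to the protocol article.

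- **AE definition (Adverse events).** AEs are unfavourable events "that occur in test subjects who have received a clinical trial intervention and do not necessarily have a causal relationship" with the intervention. No causal link is needed, but receipt of an intervention is.
- **SAE definition (Adverse events).** SAEs are "any of the following AEs that occur as a result of clinical trial intervention", followed by three outcome criteria covering death or threat to life, hospitalisation, and lasting or serious disability.
- **Reporting rule (Adverse events, second paragraph).** All SAEs in the study period "must be reported to the PI within 24 hours, regardless of whether they are related to the intervention or not". A written report to the client within 5 days and an instruction to halt also follow from an SAE. Separate 7- and 15-day clocks apply to events described by seriousness and unexpectedness.
- **Final report (Adverse events).** For each SAE it should give, where possible, its "severity, treatment, course, and causal relationship with the intervention".
- **Safety evaluation.** "AE that occurred during the study period will be listed and thoroughly explained", SAEs are described in full, and "The frequency of AE associated with and unrelated to the intervention will be recorded" and summarised descriptively.

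**The concern.** There are two separate faults.

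The first is a contradiction. One sentence makes causation a condition of being an SAE; the reporting rule and the final-report item treat causation as something still to be judged once an event is an SAE. Staff facing a hospital admission that they think unrelated get a different answer depending on which sentence they follow.

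The second is one of scope. The AE definition is tied to having received a trial intervention, and the comparator is usual care with nothing added. It is therefore unclear whether an event in a control participant is an AE at all.

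Safety is a stated aim of the trial, alongside efficacy and economic impact. In an add-on comparison with usual care, the event frequency under MARS-PD can be interpreted only against the frequency in controls. That needs one definition applied in the same way in both arms, with relatedness kept apart from seriousness.

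**Working it through.** The point rests on no sample size, power or event figure, so there is nothing to recompute. The check is to apply the written rules to concrete cases.

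**1. A MARS-PD participant is admitted to hospital and the admission is judged unrelated.**

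- AE definition: met. The participant received the intervention and no causal link is required.
- SAE definition: not met. The hospitalisation criterion is satisfied, but the event did not result from the intervention.
- Reporting rule: it covers SAEs that are related and SAEs that are not. Under the definition the second group is empty, so the words "regardless of whether they are related to the intervention or not" have no effect.
- Final-report item on causal relationship: under the definition it can have only one answer.
- Safety evaluation: the event stays in the AE listing and count, but drops out of the set of SAEs to be described in full.

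The definition and the reporting rule therefore cannot both be given effect. This conflict lies wholly within one section.

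**2. The same admission occurs in a control participant.** The answer depends on what intervention means.

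- *Narrow meaning (MARS-PD only).* Study design and setting says controls receive no additional intervention, and Economic evaluation contrasts the trial's intervention with usual care. On this meaning the event is not an AE. Since SAEs are a subset of AEs, it is not an SAE either. This would apply to 44 of 88 planned participants (44/88 = 50%).
- *Wide meaning (whatever the assigned arm provides).* The full-analysis-set rule in Statistical analysis removes subjects who did not receive the protocol's intervention. On the narrow meaning that would remove every control, so there the word must be able to include usual care. Safety evaluation lists AEs by study period with no restriction by arm. On this meaning the event is an AE, but it is an SAE only if attributed to what the control arm provides.

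The causal condition thus causes trouble on either meaning. The control-arm gap in the AE definition arises only on the narrow one.

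**3. Do both definitions contradict the reporting rule?** No. The AE definition expressly does not require causation, so it is consistent with a rule covering related and unrelated events. Its fault is confined to the restriction to recipients.

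**The case against.** The strongest reply is that the intent is plain. The reporting rule, the final-report item and Safety evaluation all treat relatedness as something recorded separately, so the causal phrase in the SAE definition looks like loose drafting. That is a fair account of intent, and nothing suggests a wish to filter events. But the definition is the rule that decides which events enter the SAE set, and as written it excludes unrelated ones.

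On controls, the reply has more force. Besides the full-analysis-set rule and Safety evaluation, Participant timeline speaks of treatment in both groups according to assignment. The Interventions section describes both arms and offers all willing participants a smart band and lifestyle guidance. Control events may well be collected in practice. What stands is an ambiguity, not a stated exclusion.

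Three stronger readings are tempting, and the article does not support them:

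- *That the control event rate is zero by construction.* This needs the narrow meaning throughout, and the article does not use the word consistently.
- *That unblinded treating staff decide causality before an event counts as serious.* The Adverse events section does not say who judges causality. SAEs go to the principal investigator, who is not said to deliver treatment, and the term test staff also covers the blinded evaluation staff.
- *That the number of lost or distorted events can be estimated.* No background event rate is given, and any figure would rest on an invented one.

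**Conclusion.** The SAE definition is wrong as written. It makes causation a condition, while the reporting rule and the final-report item in the same section presuppose that unrelated SAEs exist. This part depends on no assumption beyond the ordinary meaning of the words, and it affects how serious events are classified for any of the 88 planned participants.

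The AE definition is a lesser and separate fault. Read literally, and only if intervention means MARS-PD alone, it omits events in the 44 controls. Other sections point to a wider meaning, so the right description is unclear scope.

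No numerical effect on the safety results can be given. The point should be corrected because safety is a stated aim and the wording is cheap to repair.

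**What to change.** 1. Remove the causal condition from the SAE definition, so that seriousness rests on the outcome criteria alone. Record relatedness as a separate item for every AE and SAE.
2. Remove the restriction to recipients of an intervention from the AE definition. State that AEs and SAEs are collected in all randomised participants in both arms over the study period and tabulated by arm.
3. Reconcile with the corrected definition every step that depends on these terms: the 24-hour report to the principal investigator, the 5-day written report to the client, the halt instruction, and the 7- and 15-day clocks. Those clocks are worded once for events that are serious and unexpected and once for events that are serious or unexpected, so that wording needs settling too. How these steps should operate is for the sponsor to decide; no clinical rule is proposed here.

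The cost is a wording amendment through the ethics-board route in Study protocol modifications, and use of the same AE form in controls. More events may meet the SAE definition, and because reporting and the halt instruction depend on that term, step 3 should be done together with step 1.

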### Ethics and dissemination

This study’s protocol was approved by the Institutional Review Board of Daejeon Korean Medicine Hospital (DJDSKH-21-BM-11), and it has been registered on CRIS (no.: KCT0006646) and ClinicalTrials.gov’s PRS (no.: NCT05621772). The details of the trial will be communicated to all participants. Prior to enrollment, all participants will be required to submit a written ICF.

### Study protocol modifications

When modifying this protocol, the date, details, and reason for revision must be reported to and approved by the IRB. If the protocol is modified, the study participants will be informed.

## Discussion

PD is becoming a global health concern, and it imposes a significant individual, social, and economic burden [2,27,28]. PD is a neurodegenerative disorder with a high prevalence, particularly among the elderly, and the number of patients is rapidly increasing as the global population ages. Furthermore, even after adjusting for age, the prevalence of PD continues to rise, particularly in developed countries with a high sociodemographic index [28]. Although the mechanism is unknown, smoking has been linked to a lower risk of PD. Because smoking prevalence is declining in many countries, the future incidence of PD may be higher than previously estimated [29].

PD is a movement disorder characterized by the progressive degeneration of dopaminergic neurons in the substantia nigra pars compacta. The primary treatment option for PD is dopamine-based drug therapy [30]. Early initiation of dopaminergic therapies may alleviate symptoms, reduce disability, and improve quality of life in PD patients, but it has no disease-modifying effect. Complications of long-term levodopa therapy, such as motor fluctuations and dyskinesia, are also a source of concern [31].

There is an increasing demand for the development of new therapeutic approaches because there is currently no treatment that can reverse the primary pathology of PD. In a survey of PD patients, 94 out of 123 patients (76%) used complementary and alternative therapies such as acupuncture and herbal medicine to relieve motor symptoms, fatigue, pain, and constipation [32]. Furthermore, the importance of exercise in PD patients is becoming more widely recognized. Several systematic reviews and meta-analyses have found that exercise interventions such as resistance training, endurance training, balance training, and aerobic exercises can improve motor symptoms, muscle strength, cardio-respiratory fitness, gait performance, and balance in people with PD [33–35].

Acupuncture [36–38] and exercise [39,40] have both been shown in recent studies to have potential neuroplastic and neuroprotective effects in PD Prior to this study, we established a complex therapy (MARS-PD) to enhance the synergistic effects of acupuncture and exercise [16]. The goal of this randomized controlled trial is to assess MARS-PD’s clinical efficacy, safety, and cost-effectiveness. Because the goal of this trial is to assess the add-on effect of MARS-PD, we will use usual care as the comparator. Previous case study [17] and observational study [in review] by the authors found MARS-PD to be safe and beneficial to Parkinson’s disease patients. This study, we believe, will enable us to verify the efficacy of MARS-PD in greater detail.

## Abbreviations

A-CRO: Academic Contract Research Organization
AEs: Adverse Events
ALT: ALanine Transaminase
AST: ASpartate Transaminase
BPM: Beats Per Minute
CEAC: Cost Effectiveness Acceptability Curve
COMT: catechol-O-MethylTransferase
CRF: Case Reporf Forms
CRIS: Clinical Research Information Service
DMC: Data Monitoring Committee
EMR: Electronic Medical Records
EQ-5D: EuroQol Five Dimensions
EQ-VAS: EuroQol Visual Analogue Scale
FAS: Full Analysis Set
fNIRS: Functional Near-InfraRed Spectroscopy
HY: Hoehn and Yahr
ICF: Informed Consent Form
IPAQ: International Physical Activity Questionnaire
IRB: Institutional Review Board
L-dopa: Levodopa
MAO-B: MonoAmine Oxidase B
MARS-PD: Meridian Activation Remedy System for Parkinson’s Disease
MDS-UPDRS: Movement Disorder Society-sponsored revision of the Unified Parkinson’s Disease Rating Scale
MFDS: Ministry of Food and Drug Safety
MMSE: Mini-Mental State Exam
NIKOM: National Institute for Korean Medicine Development
PD: Parkinson’s Disease
PDSS: Parkinson’s Disease Sleep Scale
PI: Principal Investigator
PP: Per-Protocol
PSQ: Parkinson Self Questionnaire
QALY: Quality Adjusted Life Years
REM: Rapid Eye Movement
SAEs: Serious Adverse Events
SPIRIT: Standard Protocol Recommendations for Interventional Trials
TUG: Timed Up and Go
